### **8.3.3.4 Transcription of Safety Information to the CRF; Causality Assessment**

At each visit, the Investigator will perform a physical examination and will interview the subject for any solicited reactions and unsolicited AEs recorded in the DC, as well as regarding any other AEs that may have occurred. All relevant data will be transcribed into the CRF according to the instructions provided with the CRF.

The **action taken** to treat a solicited reaction or any AEs will be classified in the CRF using the following scale:

---

a European Directive 2001/21/EC, for trials conducted in Europe only

0 = No action.

1 = Medicationa.

2 = Health care contact (defined as: physician/nurse telephone contact; physician/nurse evaluation; emergency visit/outpatient hospitalization or tel. contact).

3 = Health care contact and prescription of a new medication.

4 = Hospitalization (inpatient).

The Investigator will assess the **causal relationship** between each unsolicited AEb and vaccination as either not related or related, based on the following definitions:

**0 Not related / No relationship:** The AE is clearly/most probably caused by other etiologies such as subject's underlying condition, therapeutic intervention or concomitant therapy, or the delay between vaccination and the onset of the AE is incompatible with a causal relation, or the AE onset is before vaccination.

**1 Related:** There is a reasonable possibility that the AE was caused by the vaccine. The expression "reasonable possibility" is meant to convey in general that there are facts (evidence) or arguments to suggest a causal relationship (ICH Guidelines. Clinical Safety Data Management E2A).

#### ***Serious Adverse Events (see Section 9.1 for information on SAE reporting)***

Information on SAEs will be collected and assessed throughout the trial.

The SAEs will be reported by the Investigator using SAE Reporting Forms (the procedure for reporting SAEs is described in Section 9.1). Any relevant information concerning the SAE is to be reported on this form, and if relevant information became available later, the form that was sent initially must be updated (e.g. outcome, medical history, results of investigations, copy of hospitalization reports). The Investigator will assess the causal relationship between the SAE and the vaccine with the scale provided above.

#### **8.3.4 Handling of Missing Data and Outliers**

Missing safety data will not be replaced. All vaccinated subjects with safety data, and all safety data recorded in the CRFs will be included in the safety analyses. No search for outliers will be performed.

---

a Self-medication, such as over the counter medication.

b By convention, all solicited events will be considered as related to vaccination and referred to as reactions. For these reactions, the investigator's opinion will not be requested in the CRF.

## 9 Serious Adverse Events

### 9.1 Reporting of Serious Adverse Events

In order to comply with current regulations on SAE reporting to Health Authorities and to allow the Sponsor to conduct a detailed analysis of the safety of the developed products, the Investigator will accurately document any SAE, in accordance with the notification deadlines stated below, to provide the Sponsor with all necessary information and, if requested by the Sponsor, to give access to source documents.

#### 9.1.1 Initial Reporting by the Investigator

The Investigator must report every SAE occurring during a subject's participation in the trial to the Sponsor's Global Pharmacovigilance Department (GPVD) within 24 hours of finding out about the SAE. The SAE must be reported even if the Investigator considers that the SAE is not related to the vaccine.

The Investigator must complete the "SAE Reporting Form" and send it by facsimile to the Sponsor's Pharmacovigilance department at the following number:

[contact]

If no fax machine is available, the notification of the SAE should be made by telephone to the Local Medical Manager. The Investigator will then send the completed 'SAE Reporting Form' by express mail to the following address:

Global Pharmacovigilance Department  
Sanofi Pasteur SA  
[name]  
[name]  
France

#### 9.1.2 Follow-up Reporting by the Investigator

If further relevant information concerning the SAE becomes available later (e.g., outcome, precise description of medical history, results of the investigation, copy of hospitalization report), the SAE Reporting Form sent initially must be completed and the box "Follow-up Reporting Form" must be ticked on the form. It must be reported to the Sponsor's Global Pharmacovigilance Department within 24 hours after the Investigator becomes aware of the new information. The SAE Reporting Form will be sent by fax or express mail as described above for the Initial Reporting.

The anonymity of the subjects must always be respected when forwarding this information.

### 9.1.3 Reporting of SAEs Occurring After Subject Trial Termination

Any SAE occurring after subject trial termination but likely to be related to the product must also be reported by the Investigator as soon as he/she is alerted of it. In such a case, the procedure to be followed to report the SAE to the Sponsor is identical to that described above.

### 9.1.4 Causal relationship

The causal relationship between the SAE and the product (yes or no) will first be evaluated by the Investigator using the following definitions:

**0 Not related / No relationship:** The AE is clearly/most probably caused by other etiologies such as patient's underlying condition, therapeutic intervention or concomitant therapy, or the delay between vaccination and the onset of the AE is incompatible with a causal relation, or the AE onset before vaccination.

**1 Related:** There is a reasonable possibility that the AE was caused by the vaccine. The expression "reasonable possibility" is meant to convey in general that there are facts (evidence) or arguments to suggest a causal relationship (ICH Guidelines. Clinical Safety Data Management E2A).

Then, according to the available information and the current medical knowledge, the Sponsor's Product Safety Officer will also assess the causal relationship to the product in collaboration with the Clinical Team Leader (CTL).

The decision to modify or discontinue the trial, or to break individual or all trial codes may be made after mutual agreement between the Sponsor and the Investigator(s).

### 9.1.5 Reporting SAEs to Health Authorities and IECs/IRBs

The Sponsor will inform health authorities of any reportable SAE according to the local regulatory requirements. Reporting to the Health Authorities will be according to the Sponsor's standard operating procedures.

The Sponsor's Responsible Medical Officer (the CTL) will notify the Investigators in writing of the occurrence of a reportable SAE. The Investigators will be responsible for informing the IECs or IRBs that reviewed the trial protocol.

### 9.1.6 Additional Information

If seizure occurs after vaccination, this will be considered as an SAE. The subject will not receive further vaccinations irrespective of his/her age if the seizure is assessed as related to the vaccination. However the subject will be monitored and followed-up for safety information.

If it can help to analyze the SAE, a blood sample (5 mL in a dry tube) can be taken.

For reported deaths, the Investigator should supply the Sponsor and the IEC/IRB with any additional requested information such as autopsy reports or terminal medical reports.

## 10 Data Collection and Management

### 10.1 Data Collection, CRF Completion

All clinical trial information will be reported by the Investigator or a designated person on a CRF designed specifically for this trial and provided by the Sponsor. The Sponsor will provide all necessary tools and instructions to complete the CRF. All CRFs must be signed by the Investigator. The Sponsor requires explanations for all missing information. Incorrect data must be crossed-out with a single line, then initialed and dated. Correction fluid or similar correction methods that mask the original data are not to be used. These rules also apply to the completion of SAE Reporting Forms, Data Correction Forms, and Complementary Information Forms.

To ensure the correct and consistent completion of the CRFs and the respect of the visit procedures, the CRF will contain the following information:

- All necessary scales for the rating of severity and causality of events (these scales are presented in Section 8.3.3).
- The trial flow-chart.
- A list of specific procedures to be followed at each visit.

In addition, detailed guidance for the completion of the CRF will be provided in a separate document.

Standard individual safety diaries, specifically designed for this trial and provided by the Sponsor, will be used by the subjects to record daily safety information between D0 and D21 after each vaccination. These diaries will include prelisted terms (see Section 8.3) and areas for free text. Subjects will be provided with diaries, rulers (for measuring the size of injection site reactions) and standard digital thermometers, and will be instructed how to use them. Severity or intensity scales will be provided in the diaries.

At each visit, the Investigator or designated person will transcribe the appropriate post-vaccination safety information (for the period since the previous visit) from the DC to the CRFs after interviewing the subject to ensure that the information is complete and correct.

### 10.2 Data Management

Data generated during the trial will be managed following two different processes, one related to clinical data, defined as all data reported in the CRF and all laboratory data, and one related to the data pertaining to SAEs (i.e. data reported by the Investigator on the SAE Reporting Forms and Complementary Information Forms).

#### *Clinical Data Management*

During the trial, through regular data collection and monitoring, clinical data reported in the CRFs will be integrated into the clinical database under the responsibility of sanofi pasteur Clinical Data Management platform. For each batch of data, double entry, quality control and triggers to computerized logic and/or consistency checks will be systematically applied in order to detect

errors or omissions. Medical safety data reviews may be performed several times during the course of the trial. Queries will be generated and submitted through Data Clarification Forms to the Investigator for resolution. Each step of this process will be monitored through the implementation of individual passwords and regular backups to maintain appropriate database access and to ensure database integrity.

The validation of the immunogenicity data will be performed at the laboratory level following the laboratory's procedures. Information from the laboratories such as subject identifiers and dates or sample numbers will be checked for consistency before the integration into the clinical database. All immunogenicity data, with the exception of those from the observational endpoints, will be provided by GCI, entered into GCI Laboratory Information Management Systems (LIMS) and quality control checked. These data will then be exported to Clinical Data Management for integration into the clinical database.

After integration of all corrections in the complete set of data, and after the SAE information available from Clinical Data Management and Pharmacovigilance has been reconciled, the database will be locked and saved before being released for statistical analysis.

### ***SAE Data Management***

During the trial, data pertaining to SAEs reported on SAE Reporting Forms, and Complementary Information Forms will be integrated into the Sponsor's centralized GPVD database.

Upon receipt of an SAE Reporting Form, the data will be entered into the GPVD database after a duplicate check. Each SAE is assigned a case identification number. Entered data will be independently verified against the original SAE forms. All SAEs are then reviewed by the Product Safety Officer and the CTL. Complementary Information Forms are issued and sent to the Investigator as required. Each SAE is reviewed, locked and approved in the GPVD database before being reported to the relevant authorities as necessary. Any follow-up information concerning a locked and approved SAE will be incorporated and a new version of the SAE will be created.

The data on SAEs in the Clinical Data Management database will be reconciled with those in the Pharmacovigilance database.

## **11 Statistical Methods and Determination of Sample Size**

Data in the Clinical Data Management Database will be analyzed by the Biostatistics Platform of sanofi pasteur, France, with SAS software, Version 8.2 or above (SAS Institute, Cary, North Carolina, USA).

A first statistical analysis will be performed once all the data obtained 21 days after the second vaccination have been locked (first partial database lock), to address the safety and immunogenicity objectives of the D0 to D42 period.

A final statistical analysis will be performed when all the data obtained 21 days after the booster vaccination have been locked (second partial database lock), to address the immunogenicity and safety objectives for the booster vaccination and the Ab persistence objective.

An addendum will be produced after the final 6 month safety follow-up (final database lock).

## 11.1 Statistical Methods

All the main analyses will be descriptive; for the main parameters, 95% CIs of point estimates will be calculated using normal approximation for quantitative data and exact binomial distribution (Clopper-Pearson method) for proportions.

### 11.1.1 Hypotheses and Statistical Methods for the Safety Endpoints

#### 11.1.1.1 Hypotheses

No statistical hypotheses will be tested.

#### 11.1.1.2 Safety Analysis

The safety analysis will report the occurrence of solicited reactions and the incidence of unsolicited events over the safety observation period by vaccine formulation and by age group. The safety observation period is 21 days after each vaccination, and 7 days after each vaccination for the solicited reactions.

In order to avoid any under-estimation of the incidences, the number of subjects with documented safety will be used as denominator of the frequencies. For solicited reactions, safety summary parameters and EMEA safety criteria, 95% CIs of point estimates of proportion will be calculated using the exact binomial distribution (Clopper-Pearson method) for proportions (23).

***Safety combined for the 21 days after the first two vaccinations and after each separate vaccination (including booster):***

The analyses of safety will address the number and percentage of subjects, by vaccine formulation and by age group, experiencing injection site or systemic AEs until 21 days after each injection (solicited reactions from D0 to D7 and unsolicited AEs/reactions until D21).

The number and percentage of subjects experiencing the following will be described by vaccine formulation and by age group:

- Each solicited and unsolicited (MedDRA preferred term) reaction or event after each injection.
- Each solicited reaction (from 0 to 7 days) after each injection according to severity, time to onset, and number of days of occurrence.
- Each unsolicited adverse reaction (MedDRA preferred term) (until 21 days) after each injection according to severity, time to onset, and duration.

(Specific solicited reactions for each age group will be presented separately).

Additionally, for subjects aged  $\geq 2$  years, the number and percentage of subjects experiencing the following reactions (MedDRA Preferred Terms) in the 3 days following each injection will be reported by vaccine and age group after each injection (as defined in the Note for Guidance on Harmonization Requirements for Influenza Vaccines [CPMP/BWP/214/96]):

- Injection site induration  $>5$  cm observed for more than 3 days.
- Injection site ecchymosis (hemorrhage).

- Pyrexia: rectal equivalent temperature  $>38^{\circ}\text{C}$  for  $\geq 24$  hours (pyrexia).
- Malaise.
- Shivering (chills).

The number and percentage of subjects in each group experiencing SAEs will be collected throughout the study.

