## 2.1 Endpoints

### *Safety*

- Occurrence, nature, (Medical Dictionary for Regulatory Activities [MedDRA]), duration, severity, and relationship to vaccination for any unsolicited systemic adverse events (AEs) reported in the 30 minutes after each injection.
- The occurrence, time to onset, number of days of occurrence, severity, and seriousness of solicited (prelisted in the subject diary and Case Report Form [CRF]) injection site reactions and systemic reactions occurring within 7 days following each injection will be reported (including the booster injection).
- The occurrence, nature (MedDRA preferred term), severity, relationship to vaccination and seriousness of unsolicited (spontaneously reported) adverse events within 21 days following each injection will be reported (including the booster injection).
- The occurrence, nature, time to onset, and relationship to vaccination of serious adverse events (SAEs) during the whole study period will be reported.
- The occurrence of the following reactions (MedDRA Preferred Terms given in parentheses) in the three days following each injection will be more especially reported (as defined by the EMEA Note for Guidance [CPMP/BWP/214/96]) (including the booster injection)a.
  - Injection site induration >5 cm observed for more than 3 days.
  - Injection site ecchymosis (injection site hemorrhage).
  - Rectal equivalent temperature >38°C for 24 hours or more (pyrexia).
  - Malaise.
  - Shivering (chills).

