***Adverse Reaction (AR):***

All noxious and unintended responses to a medicinal product related to any dose should be considered adverse drug reactions.

(The phrase "responses to a medicinal product" means that a causal relationship between a medicinal product and an AE is at least a reasonable possibility).

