#### **8.3.2 Endpoints**

- Occurrence, nature, (MedDRA preferred term), duration, severity, and relationship to vaccination for any unsolicited systemic adverse events reported in the 30 minutes after each injection.
- The occurrence, time to onset, number of days of occurrence, severity, and seriousness of solicited (prelisted in the subject diary and CRF) injection site reactions and systemic reactions occurring within 7 days following each injection will be reported (including the booster injection).
- The occurrence, nature (MedDRA preferred term), severity, relationship to vaccination and seriousness of unsolicited (spontaneously reported) AEs within 21 days following each injection will be reported (including the booster injection).
- The occurrence, nature, time to onset, and relationship to vaccination of serious adverse events (SAEs) during the whole study period will be reported.
- The occurrence of the following reactions (MedDRA Preferred Terms given in parentheses) in the three days following each injection will be more especially reported (as defined by the CHMP Note for Guidance [CPMP/BWP/214/96]) (including the booster injection)a:
  - Injection site induration >5 cm observed for more than 3 days.
  - Injection site ecchymosis (injection site hemorrhage).
  - Rectal equivalent temperature >38°C for 24 hours or more (pyrexia).
  - Malaise.
  - Shivering (chills).

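### Severity is an endpoint for all unsolicited adverse events, but Section 11.1.1.2 lists a severity breakdown only for unsolicited adverse reactions, which as defined means events judged related

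*Protocol*

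**What the plan says.** The endpoint appears in the synopsis, Section 2.1 and Section 8.3.2. In Section 2.1 it covers "severity, relationship to vaccination and seriousness of unsolicited (spontaneously reported) adverse events within 21 days following each injection", together with occurrence and nature. Section 8.3.2 repeats it: "severity, relationship to vaccination and seriousness of unsolicited (spontaneously reported) AEs within 21 days following each injection". The subject is adverse events, and relationship is one of the things to report about them.

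Section 11.1.1.2 then lists three descriptions by formulation and age group:

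1. "Each solicited and unsolicited (MedDRA preferred term) reaction or event after each injection", with no mention of severity.
2. Solicited reactions from day 0 to day 7, by severity, time to onset and number of days.
3. "Each unsolicited adverse reaction (MedDRA preferred term) (until 21 days) after each injection according to severity, time to onset, and duration".

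Section 8.3.1 defines an adverse reaction: "All noxious and unintended responses to a medicinal product related to any dose should be considered adverse drug reactions". It adds that this means causality is at least a reasonable possibility. Section 8.3.3.4 has the investigator classify the link between each unsolicited event and "vaccination as either not related or related, based on the following definitions".

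**The concern.** The events whose severity is an endpoint form a wider set than the events whose severity is tabulated. What separates the two sets is the investigator's causality judgement. The trial is open (Section 5.1.1), blinding is not applicable (Section 6.7), and the investigator uncovers the allocation on the scratch list at the first vaccination visit (Section 5.1.3). A judgement made with knowledge of formulation and dose would therefore decide which unsolicited events are shown by severity.

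Safety is the first-listed objective, and Section 5.2 gives safety data in children as a main reason for the trial. A reader of the report would expect to see how severe the unsolicited events were, whatever their attribution, and then which of them were thought related.

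**Working it through.** **The plan's own figure.** Section 11.3 gives the only quantitative safety statement: more than 90% probability of detecting an event of 1% incidence with 240 subjects, and 70% with 120. Both reproduce from 1 − (1 − p)^n:

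- 1 − 0.99^240 = 91.0%
- 1 − 0.99^120 = 70.1%

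These concern seeing any event at all. Unrelated events still enter the occurrence count, so the point does not disturb them. The rest is a comparison of text.

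**Step 1: scope.**

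| Item | Events covered | Severity shown? |
|---|---|---|
| Endpoint, Sections 2.1 and 8.3.2 | All unsolicited adverse events to day 21 | Yes |
| 11.1.1.2, first bullet | Reactions or events | No |
| 11.1.1.2, second bullet | Solicited reactions | Yes |
| 11.1.1.2, third bullet | Unsolicited adverse reactions | Yes |

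No row of 11.1.1.2 gives severity for an unsolicited event that is not a reaction.

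**Step 2: does reaction carry its defined meaning?** Section 8.3.1 defines the term through causality. Its footnote on injection-site events calls them all reactions because they are considered related. A footnote to the causality assessment in 8.3.3.4 says the same of solicited events. Section 11.1.1.2 names both categories when it means both: the first bullet does so, and the sentence introducing the list has "unsolicited AEs/reactions until D21". A programmer working from these definitions would restrict the third bullet to related events.

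**Step 3: which events are affected?**

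- Injection-site events are related by convention, so none drop out.
- Solicited reactions are related by convention and have their own severity table.
- Serious adverse events are reported whatever their causality (Section 9.1.1) and are counted separately in 11.1.1.2.
- What remains is non-serious, unsolicited, systemic events judged unrelated. They keep their count by preferred term and lose the breakdown by severity, onset and duration.

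**Step 4: an example.** Vomiting is solicited below 2 years (Table 8.3) but is not in the list for 2 years and above (Table 8.4). Group 3 runs from 6 to 35 months. Vomiting on day 3 in an 18-month-old is a solicited reaction and appears by severity. The same event in a 30-month-old in the same arm is unsolicited. If it is non-serious and judged unrelated, its severity appears in no listed table.

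**Step 5: size.** With n subjects, a proportion p having such an event and a share q of those judged unrelated, about n × p × q subjects lose the breakdown. The protocol gives neither p nor q. The share q could lie anywhere from none to all, so no figure follows.

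**The case against.** The strongest reply is that this is one loosely chosen word. The protocol often mixes the two terms: the heading for unsolicited events in 8.3.1 pairs AE with ADR, and the definition of a solicited reaction switches between reaction and event. The phrase unsolicited adverse reaction has no definition of its own. The bullets in 11.1.1.2 are also not a one-to-one rendering of the endpoint. They list no table by relationship or seriousness, and they add onset and duration, which the 21-day endpoint does not name. Sections 2.1 and 8.3.2 still promise that severity will be reported, nothing withdraws that promise, and a statistical analysis plan could supply the table.

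Part of this stands. A drafting slip is quite possible, and a deliberate filter cannot be inferred. But the protocol does more here than leave a table to a later plan: it specifies the severity table and gives it a narrower scope than the endpoint. If the wording is a slip, it still needs correcting, because its defined meaning produces a different table.

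Two stronger readings are tempting. A reader might infer that severe events judged unrelated disappear from the safety report. They do not: they remain in the occurrence table and in the overall counts of subjects with systemic adverse events, and serious events are reported separately. A reader might also infer that severe-event rates are understated by a known amount, or more in one arm than another. The documents give no rates and no evidence of differential attribution. The third bullet works by preferred term, and 11.1.1.2 plans confidence intervals for solicited reactions, safety summary parameters and the EMEA criteria, not for this table. A pooled severe-event rate with an interval would not be an output of this plan.

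**Conclusion.** The mismatch is in the current text and the point holds within the limits of step 3. Followed as written and as defined, Section 11.1.1.2 does not deliver the severity endpoint for non-serious unsolicited systemic events that the investigator judges unrelated.

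The consequence is confined to description. The trial tests no hypotheses (Section 11.1.1.1), and the safety review before each step down in age concentrates on serious events and severe fever (Sections 5.1.2 and 5.2), so it does not rest on this table. The size cannot be estimated from the documents.

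The conclusion assumes that reaction in the third bullet has its Section 8.3.1 meaning, and that no document outside the protocol already adds a severity table for all events. It is worth correcting because the endpoint is explicit, the trial is open and the data are already in hand.

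**What to change.** Reword the third bullet of Section 11.1.1.2 to match Sections 2.1 and 8.3.2, for example: *Each unsolicited adverse event (MedDRA preferred term), up to 21 days following each injection, by severity, time to onset and duration, for all events and separately for those assessed as related.* Any statistical analysis plan should use the same scope.

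The cost is one line of text and one more descriptive table. Severity and start and stop dates are recorded for every unsolicited event (Section 8.3.3.3), and relationship is assessed for each (Section 8.3.3.4), so nothing new has to be collected.
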